### Sample size

As this is a feasibility study, no formal sample size calculation was performed [35]. Instead, this study follows sample size recommendations for pilot randomized controlled trials [36] and aims to have at least 12 participants per group who provide full data. We aim to recruit 15 participants for each group (i.e., total sample size of 30) to compensate for a 20% dropout. This number of participants is deemed adequate to provide sufficient information on key feasibility issues such as recruitment and acceptability of the intervention.

### Recruitment

Potentially eligible participants will be identified by the clinical care team of Frailty Ambulatory Clinics at the Hospital of the Medical School, University of Sao Paulo. This team will undertake the initial approach, explaining how the study will be conducted. If the participant is willing to participate, a suitably qualified person will then provide verbal and written information about the study.

### Randomization

Participants will be randomly assigned to the EG and CG, with an allocation ratio of 1:1. Randomization schedule will be prepared from a computer-generated list of random numbers, by a researcher not involved in the trial. In order to guarantee the balance between the groups regarding the level of frailty, we will stratify pre-frail and frail participants in the randomization.

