### Statistical analyses

A detailed analysis plan will be prepared before all the data has been collected. Analyses will be conducted in Dell™ Statistica (version 13.0) using the principles of intention-to-treat. Descriptive statistics will be used to characterize the groups at baseline and present the feasibility outcomes. Although determining differences in clinical outcomes between the two groups is not the primary purpose of this trial, comparisons will be undertaken to investigate the feasibility of studying these outcomes and calculate estimates for the likely effect sizes and 95% confidence intervals. The effect size will be calculated in order to determine whether change can be detected over time using these outcome measures and to determine the most appropriate primary outcome. The focus of the results will be on the estimates of the treatment effects rather than statistical significance, and as such, no hypothesis testing will be undertaken [37]. Differences between the two comparison groups will be presented in the form of an unadjusted mean difference for continuous outcomes with their associated 95% confidence intervals.

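### Randomisation is stratified by frailty level, but the planned between-group estimate is unadjusted and ignores the stratum

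*Protocol article*

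**What the plan says.** The Randomization section of the protocol article sets a 1:1 ratio and describes how the sequence is made: "Randomization schedule will be prepared from a computer-generated list of random numbers, by a researcher not involved in the trial". It then adds the stratification and its purpose: "In order to guarantee the balance between the groups regarding the level of frailty, we will stratify pre-frail and frail participants in the randomization". The article names no blocks, minimisation or other restriction within the strata, and excludes none.

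The Statistical analyses section fixes the estimator: "Differences between the two comparison groups will be presented in the form of an unadjusted mean difference for continuous outcomes", with 95% confidence intervals and no hypothesis tests. It announces a detailed analysis plan, which is not shown. The Sample size section gives the scale: "We aim to recruit 15 participants for each group (i.e., total sample size of 30) to compensate for a 20% dropout". Trial status reports that about half of the participants had been recruited.

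**The concern.** A factor used to stratify the randomisation normally belongs in the analysis. Here it is used in the first and dropped from the second.

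The statement about balance also claims more than stratification alone can give. Independent 1:1 draws made separately for pre-frail and frail participants have the same distribution as independent 1:1 draws from one list. Balance comes from a restriction inside each stratum, and the article does not state one.

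What is at stake is the quality of the effect sizes and intervals. The article says it will use them to see whether change can be detected and to choose the most suitable primary outcome for a later trial. With about 15 per arm, lost precision or a chance shift from frailty imbalance is not negligible.

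**Working it through.** **Inputs from the article.** 1:1 allocation; strata pre-frail and frail; 15 per group, 30 in total; unadjusted mean difference with 95% CI.

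**Plan's own figure.** 12 completers per group with 20% dropout: 12 / (1 − 0.20) = 15 per group, 30 in total. This reproduces.

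**Assumptions (not in the article).** Frail/pre-frail splits of 15/15, 13/17, 10/20 and 8/22. A frailty effect g (frail minus pre-frail outcome, in within-stratum SD) of 0.5 to 1.5.

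**Branch A: allocation restricted within strata** (blocks of 4, 15/15 split, g = 1).

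- With 15 per arm and 7 or 8 frail in each, the within-arm sum of squares of the stratum indicator is 2 × (7 × 8 / 15) = 7.467. Spread over 28 degrees of freedom this adds 7.467 / 28 = 0.267 g² to the residual variance.
- Unadjusted: residual variance 1 + 0.267 = 1.267; SE = √1.267 × √(2/15) = 0.411; CI width ≈ 2 × 2.048 × 0.411 = 1.68 SD.
- Adjusted: SE ≈ √(2/15) = 0.365; CI width ≈ 2 × 2.052 × 0.365 = 1.50 SD.
- Simulation of 20,000 trials agrees, giving mean widths of 1.67 and 1.49 SD. The estimate itself varies almost equally under both analyses (SD 0.370 and 0.367), so the extra width is an overstated standard error.

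| g (SD) | Coverage, unadjusted | Width, unadjusted | Width, adjusted |
|---|---|---|---|
| 0.5 | 0.956 | 1.53 | 1.49 |
| 1.0 | 0.968 | 1.67 | 1.49 |
| 1.5 | 0.985 | 1.88 | 1.49 |

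**Branch B: no restriction within strata.** Let i of a frail and j of b pre-frail participants go to the experimental group, with i ~ Bin(a, ½) and j ~ Bin(b, ½). The gap is |i/(i+j) − (a−i)/(30−i−j)|. Exact enumeration gives:

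| Frail/pre-frail | P(gap ≥ 20 points) | P(gap ≥ 30 points) |
|---|---|---|
| 15/15 | 36% | 11% |
| 13/17 | 31% | 12% |
| 10/20 | 26% | 10% |
| 8/22 | 24% | 8% |

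Simulating one unstratified list gives the same values (for example 0.363 against 0.362 at 15/15), so the strata add nothing here. With blocks of 4 within strata for all 30 participants, the gap never exceeds 9 points at any of these splits.

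Shift in the unadjusted difference = gap × g. For a 20-point gap this is 0.20 × 0.5 = 0.1 SD up to 0.20 × 1.5 = 0.3 SD.

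Over repeated randomisations (15/15, g = 1) the unadjusted estimate averages to the true value (simulated error 0.004) and its interval covers 0.952. Adjustment reduces the SD of the estimate from 0.415 to 0.378 and the mean CI width from 1.70 to 1.54 SD.

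**The case against.** The strongest reply is that nothing shows the list to be unblocked. A reader might infer a plain list from "Randomization schedule will be prepared from a computer-generated list of random numbers", but permuted blocks are also generated from random numbers, and a journal article commonly leaves block details to the full protocol. The aim of 15 per group fits a restricted list, although it does not prove one. This stands: Branch B is a conditional result and not a finding about how this trial was randomised.

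A reader might also infer that the unadjusted analysis is biased or its intervals invalid. It is neither. Over randomisations it is unbiased, with about 95% coverage under simple allocation and more than 95% under blocking. The harm is lost precision or a chance shift within the one trial that is run. If change scores are analysed, which the article does not state, part of a baseline imbalance would cancel.

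Third, this is a feasibility trial without hypothesis tests, and group differences are not its main purpose. That limits the weight of the point. A shift of 0.1 to 0.3 SD sits inside an interval about 1.7 SD wide.

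The announced analysis plan does not fully answer the point, because the article already fixes the estimate as unadjusted. That is a stated choice and not a detail left open.

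**Conclusion.** The point holds in a limited form: the analysis leaves out the factor used to stratify, and including it helps under either reading of the list. With restriction, the unadjusted interval is about 12% wider than it need be (1.67 / 1.49 = 1.12) and over-covers at about 0.97. Without restriction, a gap of 20 points or more in frail share has a chance of 24% to 36%, and each such gap moves the estimate by 0.1 to 0.3 SD. These sizes rest on 30 participants and on assumed splits and frailty effects. The interval widths use the 15/15 split and a 1 SD effect, and the gain is smaller if frailty predicts the outcomes less strongly.

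The word *guarantee* is too strong for the method as described. The documents do not support a claim that frailty balance has failed or that the sequence is faulty. The matter is modest and cheap to correct.

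**What to change.** In Statistical analyses, make the between-group estimate a mean difference with 95% CI adjusted for frailty stratum (pre-frail or frail), and report the unadjusted figure beside it. Carry this into the announced analysis plan. The cost is one model term and one degree of freedom (28 to 27 with 30 participants).

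In Randomization, replace *guarantee* by *promote*, since stratification balances only with a restriction inside each stratum, which the article does not name. The cost is one word.

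Do not ask for a new list on the assumption that the existing one is unblocked. About half of the participants are already recruited, so the balance simulated for 30 blocked participants could not be obtained. If the list is already blocked, replacing it could break open blocks. A change to the design or procedures would also need a formal amendment under the article's Protocol amendments section.

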### Blinding

Blinding of trial participants and the intervention facilitator is not possible. All outcomes will be assessed by a researcher blinded to group allocation. Participants will be asked not to disclose their allocation to the physical therapist who will participate in the assessments.

### Data collection

The participants will be interviewed regarding sociodemographic characteristics (age, gender, educational level, marital status, and family income), health (number of Fried’s criteria, number of falls in the previous 12 months, number of chronic diseases, and number of medications currently in use), and clinical conditions (postural control and balance, gait, cognition, quality of life, mood, fear of falling, and incidence of falls).

### Data management and monitoring

All electronic identifiable information will be held on a secure, password-protected database, accessible only to the research sponsor. Paper forms with identifiable information will be held in secure, locked filing cabinets within a restricted area. Participants will be identified by a code number only. Direct access to source data/documents will be required for trial-related monitoring by authorized personnel only. Personal data collected during the trial will be handled and stored in accordance with the 1998 Data Protection Act. All paper and electronic data will be retained for at least 5 years after completion of the trial.

### Statistical analyses

A detailed analysis plan will be prepared before all the data has been collected. Analyses will be conducted in Dell™ Statistica (version 13.0) using the principles of intention-to-treat. Descriptive statistics will be used to characterize the groups at baseline and present the feasibility outcomes. Although determining differences in clinical outcomes between the two groups is not the primary purpose of this trial, comparisons will be undertaken to investigate the feasibility of studying these outcomes and calculate estimates for the likely effect sizes and 95% confidence intervals. The effect size will be calculated in order to determine whether change can be detected over time using these outcome measures and to determine the most appropriate primary outcome. The focus of the results will be on the estimates of the treatment effects rather than statistical significance, and as such, no hypothesis testing will be undertaken [37]. Differences between the two comparison groups will be presented in the form of an unadjusted mean difference for continuous outcomes with their associated 95% confidence intervals.

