### Trial design

The study will be a randomized controlled, parallel group, feasibility trial. Participants will be randomly assigned 1:1 to NWFP training or usual care. Study assessments will be conducted before and after the intervention and 30 days after the end of the intervention (follow-up).

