#### Clinical outcomes

Clinical outcomes will be the following: (1) postural control, assessed by the Mini-Balance Evaluation Systems Test (Mini-BEST-Test) [27]; (2) gait, assessed by the Functional Gait Assessment (FGA) [28]; (3) cognition, assessed by the Montreal Cognitive Scale (MoCA) [29]; (4) quality of life, assessed by the Brazilian version of the Short Form 36 (SF-36) [30]; (5) mood, assessed by the Geriatric Depression Scale (GDS-15) [31]; and (6) fear of falling, assessed by the Falls Efficacy Scale (FES-I) [32].

Due to the absence of specific studies on minimal detectable change (MDC) in frailty, we will consider a change of 3.5 points in the Mini-BEST-Test [33] and 4.2 points in the FGA [34] as significant. The MDC of the other scales has not yet been established.

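### Observed effect size is the only named criterion for choosing the main trial's primary outcome, and 12 to 15 participants per arm cannot rank six outcomes reliably

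*Protocol article*

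**What the plan says.** The Statistical analyses section states: "The effect size will be calculated in order to determine whether change can be detected over time", and the sentence goes on "using these outcome measures and to determine the most appropriate primary outcome". Effect size is the only criterion given for that choice. The same section says that between-group differences are not the main purpose, that they will be reported as unadjusted mean differences with 95% confidence intervals, and that "no hypothesis testing will be undertaken".

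The candidates are the six scales under Clinical outcomes: Mini-BESTest, FGA, MoCA, SF-36, GDS-15 and FES-I.

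On numbers, the Sample size section says "As this is a feasibility study, no formal sample size calculation was performed". The study "aims to have at least 12 participants per group who provide full data", and it adds: "We aim to recruit 15 participants for each group (i.e., total sample size of 30) to compensate for a 20% dropout". That size is defended as enough to learn about feasibility matters such as recruitment and acceptability. Nothing there claims that it can discriminate between clinical outcomes. Dissemination policies and the Discussion both present the study as preparation for a definitive trial.

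**The concern.** A feasibility trial may properly help to choose a primary outcome. The difficulty is the criterion. An effect estimate from 12 to 15 people per arm is very imprecise, and comparing six such estimates means comparing their errors as well as their true values. Two consequences follow if the outcome with the largest estimate is preferred. The outcome carried forward may not be the one that responds best, and its estimate is too large on average because it was chosen for being large.

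The choice of primary outcome is one of the main things a definitive trial would inherit from this study.

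**Working it through.** **Inputs from the protocol.** At least 12 evaluable and 15 recruited per arm, 20% dropout (Sample size); allocation 1:1 (Trial design); six scales (Clinical outcomes).

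**Assumed, because the protocol does not give them.** SD of 1 (standardised scale), the true effects, and the correlation between outcomes (0.3 to 0.7). For the main-trial illustration: two-sided alpha 0.05 and 80% power.

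**Step 1: the plan's own figure.** 12 / (1 − 0.20) = 15 per arm, 30 in total. This reproduces, and the size of the pilot is not in dispute.

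**Step 2: precision of one effect.** SE ≈ √(2/n).
- n = 12: √(2/12) = 0.41. The t-based 95% half-width is 0.85, so an observed 0.5 has an interval of about −0.35 to 1.35.
- n = 15: √(2/15) = 0.37. The half-width is 0.75, giving about −0.25 to 1.25.

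**Step 3: precision of the gap between two outcomes.** SE ≈ √(2(1 − ρ) × 2/n). At n = 12 this is 0.48, 0.41 and 0.32 for ρ = 0.3, 0.5 and 0.7. At n = 15 it is 0.43, 0.37 and 0.28. True gaps of 0.1 to 0.3 SD are of this size or smaller.

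**Step 4: taking the largest of six.** Simulation with 40,000 trials per scenario and 12 per arm, selecting the largest between-group Hedges g. Bias is the mean selected estimate minus the mean true effect of the selected outcome. Ranges run over ρ = 0.3 to 0.7.

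| True effects (SD) | Best outcome picked | Mean selected estimate | Upward bias |
|---|---|---|---|
| 0.5, rest 0.3 | 31–41% | 0.80 down to 0.65 | 0.43 down to 0.27 |
| 0.5, 0.4, 0.3, 0.2, 0.1, 0 | 37–46% | 0.76 down to 0.63 | 0.40 down to 0.23 |
| 0.5, rest 0 | 59–81% | 0.62 down to 0.53 | 0.33 down to 0.13 |
| 0.8, rest 0.2 | 67–88% | 0.89 down to 0.82 | 0.29 down to 0.09 |
| all 0.3 | no best outcome | 0.75 down to 0.60 | 0.45 down to 0.30 |

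Picking at random would find the best of six 17% of the time. With 15 per arm the picture is only slightly better: 33–44% for 0.5 against 0.3, and 73–92% for 0.8 against 0.2.

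**Step 5: conditional illustration for a main trial.** When all true effects are 0.3, the largest Cohen's d at 12 per arm averages about 0.71 to 0.78 (ρ = 0.5 to 0.3), so take 0.74. The normal formula gives 2(1.96 + 0.84)² / 0.74² = 28.6 per arm, or 30 with the t distribution. At 30 per arm and a true d of 0.3, power is about 21%. A true d of 0.3 would need 2(1.96 + 0.84)² / 0.3² = 174.2 per arm, or 176 with the t distribution.

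**The case against.** **The rule may be softer than the one simulated.** The protocol does not say that the outcome with the largest effect wins. The sentence can be read as a responsiveness check that informs a judgement, and detecting change over time may mean within-group change, which was not simulated. A detailed analysis plan is promised and could add criteria. This stands as a limit on the numbers. It does not remove the point, because the protocol states this criterion and names no other.

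**Safeguards already in the text.** The focus on estimation, the 95% intervals and the absence of tests are sensible and will show the imprecision. They do not undo selection, because an ordinary interval around the largest of six estimates is not adjusted for having been chosen.

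**Stronger readings that a reader might infer.**
- That the rule mostly selects noise, or is wrong most of the time. This holds when true effects are null, similar or moderately spread. It fails when one outcome dominates, as the third and fourth rows of the table show.
- That an inflated effect will be carried into the main trial's sample size. No section sets out such a step, so the power figure is conditional.
- That the protocol misuses minimal detectable change. It says "we will consider a change of 3.5 points in the Mini-BEST-Test [33] and 4.2 points in the FGA [34] as significant", but does not apply these values to group means. The sentence reads naturally as individual change, and the word significant need not mean a test. At most this is a wording clarification, and it is not part of this finding.

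**Conclusion.** The point holds as a defect in a stated selection criterion. It is not a criticism of the pilot's size or of reporting effect sizes. If outcomes are ranked by observed effect at 12 per arm, the chance of choosing the truly best of six runs from about 31% to 88% across the scenarios with a best outcome, and is below one half when true effects are close or graded. The upward bias in the selected estimate is roughly 0.1 to 0.5 SD. These figures assume selection of the largest between-group effect, six outcomes, and the effects and correlations listed above. The mechanism does not depend on the exact values. Serious underpowering of a main trial follows only if the selected estimate is used to plan it, which the protocol does not say. The change should be made before the detailed analysis plan is finalised.

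**What to change.** In Statistical analyses:

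- Replace effect size as the criterion for the primary outcome with clinical relevance, completeness of data, floor and ceiling effects, SD, and baseline-to-follow-up correlation.
- Report effect sizes with 95% confidence intervals as description only.
- State that the main trial's target difference will come from a clinically important difference and not from the pilot estimate.

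Separately, and optionally, say under Clinical outcomes that 3.5 and 4.2 points refer to individual change beyond measurement error.

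The cost is wording only: no new data and no change in sample size. The analysis plan is still to be written and about half the participants have been recruited, so there is time. The downside is that no headline effect size will support the choice of outcome.

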### Administration of assessments

The same-trained researcher will provide the patient with a free informed consent form, which also contains information on the possible benefits that the interventions may bring and possible risks and indemnities to patients, also emphasizing that the patient can withdraw from the research at any time without any contradictions. On the same day, the evaluator will clarify all doubts regarding the research project and inform the volunteers that all data resulting from the survey will be used for scientific purposes. The same-trained researcher, blinded to treatment allocation, will evaluate all participants at three timepoints: immediately pre and post interventions and 30 days after the end of the interventions (follow-up). Participants will be asked not to inform the evaluators about the kind of intervention they have received.

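### Between-group differences in the six clinical outcomes are fixed as unadjusted, although adjusting for baseline and the frailty stratum would use data already planned and usually give tighter estimates

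*Protocol article*

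**What the plan says.** The Statistical analyses section fixes the estimator: "Differences between the two comparison groups will be presented in the form of an unadjusted mean difference for continuous outcomes", each with a 95% confidence interval. No covariate is named. The same section says that "no hypothesis testing will be undertaken" and puts the weight on estimation. The comparisons are meant to "calculate estimates for the likely effect sizes and 95% confidence intervals", and the effect sizes serve to judge whether change can be detected and "to determine the most appropriate primary outcome".

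Two other parts of the article supply information that this estimator need not use:

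- **Baseline values.** Under Administration of assessments, the blinded assessor "will evaluate all participants at three timepoints": before the intervention, after it, and 30 days later. Clinical outcomes lists the Mini-BEST-Test, FGA, MoCA, SF-36, GDS-15 and FES-I. Data collection names the same six domains.
- **Frailty stratum.** Under Randomization, "we will stratify pre-frail and frail participants in the randomization", with the aim of balancing the arms on frailty level.

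**The concern.** The design treats frailty level as important enough to balance, and it collects a baseline value of each clinical outcome. The analysis then sets both aside. Two things follow. If baseline predicts outcome, the interval is wider than it needs to be. And with 12 to 15 people per arm, a baseline difference that arises by chance passes into the reported effect.

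The stake is the use made of the estimates. Six effect sizes will be compared to help choose the main trial's primary outcome, and an outcome could look more or less responsive than it is because its arms happened to start apart.

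**Working it through.** **Inputs from the protocol.** Sample size section: at least 12 per arm with full data, 15 per arm recruited, 20% dropout. Allocation is 1:1 and the intervals are 95%.

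**Assumptions.** The protocol gives neither an SD nor a baseline-outcome correlation. Results are therefore in SD units, with equal SDs at both times, and the correlation r is varied from 0 to 0.8. The stratum is assumed to predict nothing beyond the baseline value.

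**The plan's own figure.** 12/(1 − 0.20) = 15 per arm, 30 in total. It reproduces.

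**Formulas**, with n per arm:

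- Unadjusted post-score half-width: t(0.975, 2n − 2) × √(2/n)
- Unadjusted change-score half-width: the same × √(2(1 − r))
- Adjusted for baseline and stratum (two covariates): t(0.975, 2n − 4) × √(2/n) × √(1 − r²) × √(1 + 2/(2n − 5)). The last factor is the expected cost of estimating two covariate effects. For n = 12 it is √(1 + 2/19).

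**With 12 per arm:**

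- Unadjusted post-score: 2.074 × 0.408 = 0.847.
- Adjusted at r = 0: 2.086 × 0.408 × 1.051 = 0.895. For other r, multiply by √(1 − r²).

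| r | Post-score, unadjusted | Change score, unadjusted | Adjusted for baseline and stratum |
|---|---|---|---|
| 0 | 0.847 | 1.197 | 0.895 |
| 0.3 | 0.847 | 1.002 | 0.854 |
| 0.5 | 0.847 | 0.847 | 0.775 |
| 0.7 | 0.847 | 0.656 | 0.639 |
| 0.8 | 0.847 | 0.535 | 0.537 |

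*Against post-scores*, adjustment widens the interval by about 6% at r = 0 and breaks even near r = 0.3. It narrows it by 8.4%, 24.5% and 36.6% at r = 0.5, 0.7 and 0.8. At r = 0.7 the variance falls by 1 − 0.51 × (1 + 2/19) = 0.44. In interval width this equals (0.847/0.639)² ≈ 1.75 times the sample, or about 21 per arm instead of 12.

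*Against change scores*, the gain is 1 − 0.854/1.002 ≈ 15% at r = 0.3, then about 8%, 3% and 0% at r = 0.5, 0.7 and 0.8.

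**With 15 per arm**, the unadjusted post-score half-width is 0.75. The adjusted values are 0.68, 0.56 and 0.47 at r = 0.5, 0.7 and 0.8. The cost at r = 0 is about 4%.

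**Chance imbalance.** The standard error of a baseline difference is √(2/12) = 0.41 SD, ignoring any reduction from stratification. A gap of 0.4 SD is thus about one standard error. Given such a gap at r = 0.7:

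- a post-score difference shifts by 0.7 × 0.4 = 0.28 SD;
- a change-score difference shifts by (0.7 − 1) × 0.4 = −0.12 SD, in the opposite direction.

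**Coverage check.** Simulated trials (4,000 per setting, normal data, no strata, adjustment for baseline only) gave coverage of 94% to 96% for post-score, change-score and adjusted analyses. The unadjusted intervals are therefore not invalid.

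**The case against.** The strongest reply is that this is a feasibility trial. Its protocol says that comparing clinical outcomes is not the main purpose, it tests nothing, and its sample size does not come from these effects. Even the adjusted half-width of 0.64 to 0.78 SD at r = 0.5 to 0.7 would not pin down an effect. That stands, and it limits the importance of the point. It does not remove it, because the same section uses the effect sizes to help select the main trial's primary outcome.

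A second reply also stands. The article does not say whether the difference is in post-scores or change scores. The detectable-change thresholds under Clinical outcomes, and the stated interest in change over time, make change scores a fair reading. A raw difference in change scores already uses the baseline, and adjustment then adds little once r reaches 0.7.

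Three stronger readings are tempting, and the documents do not support them:

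- **That the unadjusted estimate is biased or its interval invalid.** Over randomisation it is unbiased, and ignoring a prognostic stratum makes the interval too wide rather than too narrow. The 0.28 SD above is a shift conditional on an observed gap.
- **That adjustment would nearly double the effective sample.** That takes 1/(1 − r²) = 1.96 at r = 0.7 and leaves out the cost of two covariates. The figure is about 1.75, only for post-scores, and only if r is that high.
- **That every outcome has an unused baseline.** This is true of the six clinical outcomes. Attendance, satisfaction and adverse events have none.

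Nor does the protocol say how strongly pre-frail versus frail status predicts these outcomes, so no gain from the stratum itself is claimed.

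**Conclusion.** The point holds as a nearly free improvement of minor to moderate importance. It is not an omission left to the analysis plan that is still to come, because the article itself fixes the unadjusted form. For post-scores with 12 per arm, the half-width falls from 0.85 SD to about 0.78, 0.64 or 0.54 SD at r = 0.5, 0.7 or 0.8. There is no gain at r = 0.3, and a cost of 4% to 6% at r = 0. For change scores the gain is about 8%, 3% and 0% at r = 0.5, 0.7 and 0.8, and larger at lower r. All these sizes rest on an assumed correlation and on equal SDs.

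The case for adjustment does not depend on knowing r. It is close to the better of the two unadjusted forms, or better than both, across the range examined. It also makes the choice between post and change scores largely immaterial.

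**What to change.** In Statistical analyses, replace the unadjusted difference as the main estimate. For each of the six clinical outcomes, at post-intervention and at follow-up, report the mean difference with its 95% confidence interval from a linear model that includes the outcome's baseline value and the pre-frail/frail stratum. This can be an ANCOVA at each visit or one mixed model over both visits. Keep the unadjusted difference as supportive, and state whether it is in post-scores or change scores.

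The cost is a sentence or two of text and two degrees of freedom per model, with at most about 6% in interval width if baseline turns out not to predict outcome. No new data are needed. The article reports recruitment at about half and a detailed analysis plan still to be written, so the change can be specified in that plan.
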